## Abstract

**Background:**

Nutrition is one of the fundamentals of care provided to critically ill adults. The volume of enteral nutrition received, however, is often much less than prescribed due to multiple functional and process issues. To deliver the prescribed volume and correct the energy deficit associated with enteral nutrition alone, parenteral nutrition can be used in combination (termed “supplemental parenteral nutrition”), but benefits of this method have not been firmly established. A multi-centre, randomised, clinical trial is currently underway to determine if prescribed energy requirements can be provided to critically ill patients by using a supplemental parenteral nutrition strategy in the critically ill.

**Methods/design:**

This prospective, multi-centre, randomised, stratified, parallel-group, controlled, phase II trial aims to determine whether a supplemental parenteral nutrition strategy will reliably and safely increase energy intake when compared to usual care. The study will be conducted for 100 critically ill adults with at least one organ system failure and evidence of insufficient enteral intake from six intensive care units in Australia and New Zealand. Enrolled patients will be allocated to either a supplemental parenteral nutrition strategy for 7 days post randomisation or to usual care with enteral nutrition. The primary outcome will be the average energy amount delivered from nutrition therapy over the first 7 days of the study period. Secondary outcomes include protein delivery for 7 days post randomisation; total energy and protein delivery, antibiotic use and organ failure rates (up to 28 days); duration of ventilation, length of intensive care unit and hospital stay. At both intensive care unit and hospital discharge strength and health-related quality of life assessments will be undertaken. Study participants will be followed up for health-related quality of life, resource utilisation and survival at 90 and 180 days post randomisation (unless death occurs first).

**Discussion:**

This trial aims to determine if provision of a supplemental parenteral nutrition strategy to critically ill adults will increase energy intake compared to usual care in Australia and New Zealand. Trial outcomes will guide development of a subsequent larger randomised controlled trial.

**Trial registration:**

NCT01847534 (First registered 5 February 2013, last updated 14 October 2015)

**Electronic supplementary material:**

The online version of this article (doi:10.1186/s13063-015-1118-y) contains supplementary material, which is available to authorized users.

## Background

In critical illness, enteral nutrition (EN) is usually delivered to provide estimated daily nutrition requirements via a gastric tube [1–3]. EN is the preferred choice of nutrition for critically ill adults because it mimics normal nutritional intake in health, preserves gastrointestinal tract (GIT) function, is relatively inexpensive and has been associated with a reduced incidence of pneumonia and mortality when started early after intensive care unit (ICU) admission [4–6]. The alternative to EN is parenteral nutrition (PN), which is a specialised solution designed to provide daily nutrition requirements intravenously. PN is used when a patient does not have a functioning GIT or when a clinical preference for use of PN exists [1, 7]. Until recently it was thought that PN was associated with an increased risk of infectious complications and mortality, although new data indicates that these risks may have reduced with contemporary care in the ICU [8, 9].

It has been reported that only 45–60 % [10] of energy is provided when EN is used alone due to delivery and tolerance problems [11], resulting in failure to meet daily energy requirements with unknown consequences. The strategy of “supplemental PN” aims to correct the energy deficit from inadequately delivered EN with a supply of PN, to meet 100 % of daily energy requirements in combination. This approach is based on the premise that delivery of close to 100 % of estimated daily nutrition requirements may improve patient outcomes. Whilst the strategy has been demonstrated to deliver close to 100 % of estimated energy needs, the effects on clinical outcomes have been contradictory [12–14]. A prospective randomised control trial (RCT) which investigated supplemental PN initiated early (within 48 hours of ICU admission) versus late (8 days after ICU admission) demonstrated that late supplemental PN resulted in patients being more likely to be discharged earlier from the ICU, with fewer infections when compared to patients in the early arm. However, late supplemental PN led to a higher proportion of hypoglycaemia, a more pronounced inflammatory response and did not affect overall hospital, 90-day mortality or functional status [15]. The outcomes from this study appear to be contradictory and may relate to the use of aggressive insulin therapy, which is not practiced in Australia and New Zealand (ANZ) [16]. Furthermore, the population in this RCT were largely patients undergoing cardiac surgery, and of low to moderate acuity. This patient group can usually return to volitional oral intake quickly and do not often require artificial nutrition due to their short duration of ICU stay; thus, it would seem there may be a low likelihood of benefit from supplemental PN in this population. Another RCT investigating supplemental PN from admission to ICU versus usual care found that the supplemental PN group received more energy (28 kcal/kg per day versus 20 kcal/kg per day) and had fewer nosocomial infections compared with the usual care group (27 % versus 38 %, respectively), but only on days 9–28 of ICU admission [14]. This finding may be explained by the positive effect of adequately delivered nutrition on immunity later in the ICU stay, which is also a biologically plausible explanation.

Thus, it seems that supplemental PN in addition to standard EN may be able to deliver increased energy to critically ill adults, but the exact clinical effects and the population that may benefit most remain undefined. Our aim is to determine if a supplemental PN strategy commenced 48–72 hours following ICU admission will deliver increased amounts of energy to adults with severe critical illness, when compared with usual care in six ANZ tertiary ICUs.

## Methods

### Design and study participants

A stratified, prospective, multi-centre, unblinded, randomised, parallel-group phase II study will be undertaken.

### Inclusion criteria

Admitted to intensive care between 48 hours and 72 hours previouslyMechanically ventilated at the time of enrolment and expected to remain ventilated until the day after tomorrowAt least 16 years of ageHave central venous access suitable for PN solution administrationHave one or more organ system failure related to their acute illness defined as:PaO_2_/FiO_2_ ≤ 300 mmHgCurrently on one or more continuous vasopressor infusions which were started at least 4 hours ago at a minimum dose of:Dopamine ≥ 5 mcg/kg/minNoradrenaline ≥ 0.1 mcg/kg/minAdrenaline ≥ 0.1 mcg/kg/minAny dose of vasopressinMilrinone > 0.25 mcg/kg/min)6)Renal dysfunction defined as

In patients without known renal disease:Serum creatinine > 171 mmol/L ORCurrently receiving renal replacement therapy

In patients with known renal disease:An absolute increase of > 50 % in serum creatinine from baseline ORCurrently receiving renal replacement therapy7)Currently has an intracranial pressure monitor or ventricular drain in situ8)Currently receiving extracorporeal membrane oxygenation9)Currently has a ventricular assist device.

### Exclusion criteria

Patients will be excluded if:Both EN and PN cannot be delivered at enrolment (that is, either an enteral tube or a central venous catheter cannot be placed or clinicians feel that EN or PN cannot be safely administered due to any other reason)Currently receiving PNStandard PN solutions cannot be delivered at enrolment (that is, clinicians believe that a patient definitely needs a specific parenteral nutrition formulation (for example, glutamine supplementation or specific lipid formulation)Death is imminent or deemed highly likely in the next 96 hoursThere is a current treatment limitation in place or the patient is unlikely to survive to 6 months due to underlying illnessMore than 80 % of energy requirements have been satisfactorily delivered via the enteral route in the last 24 hoursAre known to be pregnantThe treating clinician does not believe the study to be in the best interest of the patient.

### Randomisation, allocation concealment and blinding

Concealed randomisation will be performed via a web-based system which includes randomisation in blocks of 6 at each site. Treatment allocation will be stratified by site. The trial is unblinded.

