### Study procedures common to both arms

Patients will be screened for eligibility by research coordinators/medical staff at each site when they are between 48 and 72 hours of their first admission to the ICU. Those that are found to meet all the inclusion and none of the exclusion criteria will be randomised using a web-based randomisation system.

At randomisation, the body weight of study participants will be standardised using calculated body weight (CBW). To determine CBW, actual or estimated weight and height will be required to allow calculation of body mass index (BMI). The weight used to determine BMI will be defined according to the following hierarchy:Actual body weight if it has been recorded in the previous 6 weeksEstimated dry weight if actual weight is not known.

Height will be estimated using demi arm span [17].

CBW will be the patient’s actual weight if their BMI is deemed to be <25 kg/m^2^. If their BMI is ≥25 kg/m^2^, the CBW will be set to the patient’s ideal weight at a BMI of 23 kg/m^2^. Once the CBW has been determined, it will not be changed for the study duration.

Daily energy requirements will be estimated using CBW with a fixed prescription. The daily energy requirements will be set at 25 kcal/kg CBW unless the patient is receiving renal replacement therapy (RRT) and/or extracorporeal membrane therapy (ECMO), where 30 kcal/kg of CBW will be used. The daily energy requirement will only be changed during the study period if the patient commences or discontinues ECMO and/or RRT (with the two requirement options being 30 kcal/kg CBW or 25 kcal/kg CBW, respectively). A higher energy requirement has been chosen during RRT and/or ECMO due to the potential for increased metabolic stress and inflammation associated with the delivery of both therapies and the underlying disease processes that require these treatments [18]. Once randomised, the target rate for continuous EN delivery will be calculated by the treating clinical team to match the daily energy requirement, with the assumption that all patients should receive 100 % of their daily energy requirements from administration of EN and rounded up to the nearest 5 ml/hour. The choice of EN formula, protein requirement estimation and management of blood glucose levels will be according to local protocols.

Figure 1 demonstrates the study processes from screening to study completion.

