### Sample size and power

Using two published RCTs on nutrition therapy in ANZ critically ill patients, we estimated that the usual care group would receive an average of 1,400 kcal/day. We aim to deliver an additional 420 kcal/day (using a standard deviation of 600 kcal/day) to the intervention group, which is a 30 % relative increase in energy delivery and requires a sample size of 100 patients (80 % power, significance 0.05).

This sample size will also provide baseline rates of other key secondary outcomes which could be used in the future to inform sample size estimations for larger RCTs assessing clinical outcomes.

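### One fixed block size of 6 within site, in an unblinded trial, lets a site that keeps a tally know about 20 to 24 of the 100 allocations before enrolment

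*Protocol article*

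**What the plan says.** The design is set out in the protocol article under Randomisation, allocation concealment and blinding. That section says "Concealed randomisation will be performed via a web-based system" and describes "randomisation in blocks of 6 at each site". It adds "Treatment allocation will be stratified by site" and "The trial is unblinded". One block size is given, and nothing says that it varies or that sites are not told it.

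Under Study procedures common to both arms, "Patients will be screened for eligibility by research coordinators/medical staff at each site". The people who screen therefore work where earlier allocations are visible.

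The Inclusion criteria admit patients between 48 and 72 hours after ICU admission and call for a forecast of continued ventilation. The Exclusion criteria add forecasts of early death and of survival to 6 months, a view on whether enteral or parenteral nutrition can be given safely, and the treating clinician's view of the patient's best interest.

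**The concern.** A web system hides the allocation list, but it cannot hide what follows from counting. When every block at a site holds the same known number of patients and each allocation is visible, the rest of a block is fixed once one arm has used its share. A screener who knows the next allocation can, knowingly or not, enrol, defer or pass over a particular patient. The judgement-based criteria and the 24-hour window (72 − 48) leave room for this.

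The arms could then differ in who was enrolled. The primary outcome is energy in calories and not per kilogram (Outcome measures), while the requirement scales with calculated body weight. Body size and early feed tolerance are both visible before randomisation and both bear on the outcome. Ventilation time, length of stay and mortality are exposed in the same way, and the results are meant to inform a larger trial. Under Statistical analysis plan, single-measure outcomes get unadjusted tests. Site and covariates enter only in sensitivity analyses, which cannot correct for selection on unrecorded features.

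**Working it through.** The article gives no figure for predictability, so there is none to reproduce.

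**Inputs.** Block size 6, by site, unblinded (randomisation section). 100 patients from six ICUs (abstract and Sample size and power), a mean of 100/6 = 16.7 per site. Allocation ratio 1:1, so 3:3 per block; this is an assumption, because the article does not state the ratio outright.

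**Step 1: one complete block.** A 3:3 block has 6!/(3!·3!) = 20 equally likely orderings. An allocation is certain once one arm already has its three patients.

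| Position | Condition | Probability certain |
|---|---|---|
| 1 to 3 | cannot occur | 0 |
| 4 | first three alike: 2/20 | 0.1 |
| 5 | first four split 3 and 1: 8/20 | 0.4 |
| 6 | always | 1.0 |

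The sum is 0.1 + 0.4 + 1.0 = 1.5 per block, and 1.5/6 = 25%. The closed form 2m/(m+1) with m = 3 gives 6/4 = 1.5. If blocks were 4:2, the share would be 28.9%.

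**Step 2: this trial.** Incomplete last blocks lower the share.

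- Site of 17: two full blocks plus five positions, 2 × 1.5 + 0.1 + 0.4 = 3.5.
- Site of 16: two full blocks plus four positions, 2 × 1.5 + 0.1 = 3.1.
- Four sites of 17 and two of 16 (68 + 32 = 100): 4 × 3.5 + 2 × 3.1 = 20.2.

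Over every split of 100 patients across six sites, the expected number runs from 19.9 to 24.1. For example, sites of 16, 16, 16, 16, 15 and 21 give 4 × 3.1 + 3.0 + 4.5 = 19.9. Sites of 18, 18, 18, 18, 12 and 16 give 4 × 4.5 + 3.0 + 3.1 = 24.1.

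**Step 3: guessing.** In a complete block, guessing the arm with more places left is right with probability 0.5, 0.6, 0.6, 0.7, 0.7 and 1.0 at positions 1 to 6. The mean is 4.1/6 = 68.3%, against 50% with no information.

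**Step 4: varying sizes.** Simulation (5,000 runs each) at 16, 17 and 18 patients per site. The observer knows which sizes are in use but not their order.

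| Block sizes | Certain allocations | Best guess correct |
|---|---|---|
| 6 only | 19 to 25% | 66 to 68% |
| 4, 6 | about 6% | about 68% |
| 2, 4, 6 | about 4% | about 69% |
| 4, 6, 8 | about 2% | about 67% |

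Varying the size removes most of the certainty and hardly changes the success of guessing.

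**The case against.** The strongest reply is that the risk is conditional. Staff must know the block size, keep a tally and act on it. The article does not say that sites were told the size, and rules on withholding it may sit in the full protocol, which is not shown. The trial was already underway when the article was written, so publication cannot have exposed the size for patients enrolled earlier, and the number still to come is unknown. Many criteria are measured, such as organ-failure thresholds and the 80% enteral cut-off, and the window limits how long enrolment can be deferred. The intervention raises the primary outcome directly, and sensitivity analyses for site, covariates and baseline imbalance are planned.

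Much of this stands. It limits the point to a risk, and the documents do not allow the resulting bias to be sized. It does not remove the point. The single block size is a stated choice and not an omitted detail, it is now public, and the judgement-based criteria remain alongside the measured ones.

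Three stronger readings are tempting and are not supported:

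- **25 certain allocations in the trial.** This treats every block as complete. The highest expectation for 100 patients over six sites is 24.1.
- **Concealment is contradicted.** The list stays hidden in the web system. The weakness is that it can be predicted, not that it is disclosed.
- **The 68% guess rate is a harm of the fixed size that the change would cure.** Step 4 shows that it would hardly move.

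**Conclusion.** The point holds as a design weakness of limited size. With one published block size of 6 within site and visible allocations, a site that keeps count can expect certainty for 25% of a complete block. That is about 20 of the 100 patients at 16 or 17 per site, and about 20 to 24 over possible site splits. The figures assume 1:1 allocation, knowledge of the block size and an accurate tally of past allocations. Nothing in the article shows that foreknowledge has been used, and a reader should not infer that the results are biased. The risk of selection bias is avoidable at little cost, so this counts as a cheap improvement and does not by itself put the trial's validity in doubt.

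**What to change.** For all patients still to be randomised, have the web system draw block sizes at random within each site, for example from 4, 6 and 8. Withhold the new sizes and their order from the sites until recruitment ends, and say in the protocol that sizes vary without listing them. The size of 6 is already public, so secrecy can protect only the new sequence.

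Certain allocations would fall to roughly 2 to 6% of the patients randomised under the new lists, depending on the sizes chosen (about 2% for 4, 6 and 8). The best-guess rate would stay near 66 to 69%, so the change reduces foreknowledge and does not abolish it. The total benefit depends on how many patients remain, which the article does not give.

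The cost is a new list in an existing system and slightly more possible imbalance within a site.

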### Trial intervention and comparator

The intervention is the delivery of a supplemental PN strategy using Olimel N9-840E/Triomel 9, manufactured and supplied by Baxter Healthcare Corporation, Old Toongabbie NSW 2146, Australia. A multi-trace element solution (10 ml), multi-vitamin (Cernevit, Baxter Healthcare Corporation, 5 ml) and ascorbate (300 milligrams) for stability will be added to the intervention in a Baxter Healthcare Corporation compounding centre following good manufacturing practice.

Further details on the interventional product can be viewed at Additional file 1.

The comparator arm will be usual care, with provision and management of nutrition as per local practice at each participating site.

The intervention period is defined as 7 days from the day of randomisation.

### Study procedures common to both arms

Patients will be screened for eligibility by research coordinators/medical staff at each site when they are between 48 and 72 hours of their first admission to the ICU. Those that are found to meet all the inclusion and none of the exclusion criteria will be randomised using a web-based randomisation system.

At randomisation, the body weight of study participants will be standardised using calculated body weight (CBW). To determine CBW, actual or estimated weight and height will be required to allow calculation of body mass index (BMI). The weight used to determine BMI will be defined according to the following hierarchy:Actual body weight if it has been recorded in the previous 6 weeksEstimated dry weight if actual weight is not known.

Height will be estimated using demi arm span [17].

CBW will be the patient’s actual weight if their BMI is deemed to be <25 kg/m^2^. If their BMI is ≥25 kg/m^2^, the CBW will be set to the patient’s ideal weight at a BMI of 23 kg/m^2^. Once the CBW has been determined, it will not be changed for the study duration.

Daily energy requirements will be estimated using CBW with a fixed prescription. The daily energy requirements will be set at 25 kcal/kg CBW unless the patient is receiving renal replacement therapy (RRT) and/or extracorporeal membrane therapy (ECMO), where 30 kcal/kg of CBW will be used. The daily energy requirement will only be changed during the study period if the patient commences or discontinues ECMO and/or RRT (with the two requirement options being 30 kcal/kg CBW or 25 kcal/kg CBW, respectively). A higher energy requirement has been chosen during RRT and/or ECMO due to the potential for increased metabolic stress and inflammation associated with the delivery of both therapies and the underlying disease processes that require these treatments [18]. Once randomised, the target rate for continuous EN delivery will be calculated by the treating clinical team to match the daily energy requirement, with the assumption that all patients should receive 100 % of their daily energy requirements from administration of EN and rounded up to the nearest 5 ml/hour. The choice of EN formula, protein requirement estimation and management of blood glucose levels will be according to local protocols.

Figure 1 demonstrates the study processes from screening to study completion.

**Fig. 1 Fig1:**
[figure not shown]
Study overview. CRP: C-reactive protein; EN: enteral nutrition; EQ-5D: EuroQuol 5 dimension; ICU: intensive care unit; LFTs: liver function tests; LOS: length of stay; MV: mechanical ventilation; PN: parenteral nutrition; 6MWT: 6-minute walk test

### Study procedures in the intervention arm

Day of randomisation:The interventional product will be administered to intervention patients within 2 hours of randomisation via a central venous catheter (including long-term central catheters, for example, a Hickman catheter if already in situ) or a peripherally inserted central catheter. Management of the line will be as per the participating hospital’s usual procedure. Due to the increased risk of overfeeding with energy when PN is used, the intervention strategy has been designed to minimise this risk. Thus, the maximum amount of energy provided by the intervention will be 20 kcal/kg/day (or 24 kcal/kg/day for those on RRT and/or ECMO), which equals 80 % of the daily energy requirement set at 25 or 30 kcal/kg/day, respectively. This will allow for small amounts of energy provided by EN, 25/50 % glucose and propofol (non-nutritional energy sources) in addition to interventional product in the intervention arm.

The starting rate of PN will be determined by the amount of energy received via the enteral route in the 24 hours prior to randomisation:Between 40–80 % of daily energy requirement received from EN: PN rate will equal delivery of 10 kcal/kg of CBW/day (or 12 kcal/kg of CBW/day for those on RRT and/or ECMO)Less than 40 % of daily energy requirement received from EN: PN rate will equal delivery of 20 kcal/kg of CBW/day (or 24 kcal/kg of CBW/day for those on RRT and/or ECMO).

Management of EN in the intervention arm will be according to unit protocol. Every attempt will be made by the treating clinical team to achieve delivery of EN in the intervention arm to provide 100 % of daily energy requirements. Importantly, EN must not be reduced based on the amount of intervention being administered.

Daily review of intervention:From study day 2 until study day 7 (or ICU discharge, whichever occurs first), the adequacy of energy from EN and non-nutritional sources will be assessed at midday by a member of the site research team. Total energy intake will be determined for the 24 hours prior to review and used to determine the rate of delivery of study PN for the subsequent 24 hours (Fig. 2). Once the rate is set for the following 24 hours by the research team, it should not be altered by the treating team unless deemed necessary for patient safety.

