**Fig. 2 Fig2:**
[figure not shown]
Daily adjustment of PN rate in intervention arm. ECMO: extracorporeal membrane oxygenation; EN: enteral nutrition; PN: parenteral nutrition; RRT: renal replacement therapy

Management of interruptions to EN in the intervention arm:In the event of an anticipated or actual interruption to EN for a period of 2 hours or more in the intervention arm, the interventional strategy will be adjusted to minimise energy deficit for the period of the interruption. During the interruption period, the intervention will be run at the hourly rate corresponding to 20 kcal/kg or 24 kcal/kg for those on RRT and/or ECMO. If the patient is already receiving the highest rate of the intervention, there will be no change to the rate during the interruption period. As soon as is practical, EN should be recommenced as per local protocol and the intervention returned to the rate determined as per the midday assessment.

Cessation of study intervention prior to the end of the study period:The intervention will cease either prior to ICU discharge or 7 days following enrolment if energy from EN and non-nutritional sources provides more than 80 % of estimated energy requirements on any day. Cessation on any one day will not preclude recommencement in the following 24 hours should the strategy be indicated based on the procedures previously outlined, until study day 7.Should a patient commence oral intake during the 7-day study period, the intervention will cease when it is deemed that the patient will resume oral intake with the intent to provide nutrition, that is, not only to provide water or fluid intake.

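### The 80 % threshold counts enteral energy alone for entry and the starting PN rate, but enteral plus propofol and glucose energy for the midday review and the stop rule

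*Protocol article*

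**What the plan says.** Four rules in the protocol article refer to recent energy intake.

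- **Entry** (Exclusion criteria): a patient is excluded if enteral delivery over the preceding 24 hours exceeded 80 % of requirement. Only the enteral route is named.
- **Starting rate** (Study procedures in the intervention arm, day of randomisation): "The starting rate of PN will be determined by the amount of energy received via the enteral route", counted over the 24 hours before randomisation. The bands are "Between 40–80 % of daily energy requirement received from EN: PN rate will equal delivery of 10 kcal/kg of CBW/day" and "Less than 40 % of daily energy requirement received from EN: PN rate will equal delivery of 20 kcal/kg of CBW/day", with 12 and 24 kcal/kg for patients on RRT and/or ECMO.
- **Daily review** (same section, from study day 2): "the adequacy of energy from EN and non-nutritional sources will be assessed at midday by a member of the site research team".
- **Stop rule** (paragraph on cessation, after Fig. 2): PN ceases "if energy from EN and non-nutritional sources provides more than 80 % of estimated energy requirements on any day".

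The non-nutritional sources are identified where the PN ceiling of 80 % of requirement is explained: "This will allow for small amounts of energy provided by EN, 25/50 % glucose and propofol (non-nutritional energy sources". The same paragraph says that the strategy was designed to limit the risk of overfeeding. No reason is given for counting fewer sources on the day of randomisation than on later days.

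**The concern.** Entry and stopping share the number 80 % but not the quantity it is compared with. A patient whose enteral energy is at or below 80 %, but whose enteral plus propofol and glucose energy is above it, can be randomised and started on PN while already at a level that the protocol treats as a reason to stop. All participants are ventilated at enrolment, so propofol exposure is foreseeable.

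Two things are at stake. First, the starting dose ignores energy that the protocol counts from the next day, which sits badly with the stated aim of limiting overfeeding. Second, such patients stay in the intention-to-treat comparison of mean energy over 7 days. If PN is stopped at their first review, they add less to the contrast that the trial exists to measure. As the trial is meant to guide a larger one, an entry rule that disagrees with its own continuation rule could be carried forward.

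**Working it through.** **Inputs from the protocol.** Requirement: 25 kcal/kg of calculated body weight (CBW) per day, or 30 on RRT and/or ECMO. Starting PN: 10 or 20 kcal/kg/day (12 or 24). Exclusion and stop thresholds: more than 80 %. **Assumptions.** CBW of 70 kg, used only to convert to kcal/day, and illustrative shares of non-nutritional energy (NN), for which the document gives no figures.

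**Step 1: the protocol's own figure.** The PN ceiling is 20/25 = 24/30 = 80 % of requirement, as stated. The lower band is 10/25 = 12/30 = 40 %.

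**Step 2: condition for a conflict at 80 %.** The patient is not excluded if EN ≤ 80 %, and the stop rule is met if EN + NN > 80 %. Both hold whenever NN > 80 % − EN, with EN ≤ 80 %.

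**Step 3: the two rules applied to the same intake** (% of requirement; PN expressed as a 24-hour rate, intake unchanged).

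| EN | NN | EN + NN | Starting PN | EN + NN + PN | Stop rule met by same intake? |
|---|---|---|---|---|---|
| 70 | 15 | 85 | 40 | 125 | yes |
| 75 | 10 | 85 | 40 | 125 | yes |
| 79 | 2 | 81 | 40 | 121 | yes |
| 75 | 5 | 80 | 40 | 120 | no |
| 50 | 10 | 60 | 40 | 100 | no |

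The conflict is confined to patients near the threshold. At EN 50 % with NN 10 % the rules agree.

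**Step 4: how much NN energy is needed.** The requirement at 70 kg is 25 × 70 = 1,750 kcal/day.

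- EN 79 %: more than 1 % = 17.5 kcal/day.
- EN 75 %: more than 5 % = 1.25 kcal/kg = 87.5, about 88 kcal/day (on RRT and/or ECMO, 0.05 × 30 × 70 = 105).
- EN 70 %: more than 10 % = 175 kcal/day.

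These amounts scale in proportion to CBW.

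**Step 5: what the bands give without any NN energy.** The upper edges are 80 + 40 = 120 % and just under 40 + 80, that is almost 120 %. Most of a total such as 125 % is therefore a property of the bands. Uncounted NN energy comes on top.

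**Step 6: the 40 % boundary.** With EN 35 % and NN 10 %, the starting rule gives PN at 80 % (total 35 + 10 + 80 = 125 %). If the later bands also cut at 40 %, the same intake (45 %) would give PN at 40 % at the review. The later bands are in Fig. 2, which is not shown, so this case is conditional.

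**Step 7: overlapping look-back.** The midday review looks back 24 hours. If the day of randomisation is study day 1, a patient randomised at 23:00 has a first review at 12:00 the next day, covering 11 hours before randomisation and 13 after. Those 11 hours count enteral energy only for the starting rate, and enteral plus NN energy for the review.

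**The case against.** The strongest reply is that the difference is coherent. The abstract describes patients with evidence of insufficient enteral intake, the primary outcome is energy from nutrition therapy, and propofol and glucose are labelled non-nutritional. Selecting on enteral energy fits that population, and entry and daily titration are different decisions. This stands as a possible justification for the exclusion criterion. It does not explain why the first PN rate uses a narrower base than the review and stop rules that govern the same infusion from the next day.

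A second reply is that the 80 % PN ceiling already leaves room for small amounts of other energy. The ceiling does have that purpose. However, the conflict arises in patients on the 40 % starting rate, whom the ceiling does not affect, and small amounts suffice near the threshold.

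A third reply is that consistency alone would not prevent totals above requirement, since the bands allow about 120 % and a single enteral base would leave the 70 + 15 patient at 125 % at every review. This stands. The case for change is the contradiction between rules, not a promise that one base removes the excess.

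A reader might also infer more than the text supports:

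- That every later PN decision uses the wider base. The EN-interruption rule and the oral-intake stop use no intake count.
- That affected patients get PN briefly and then little or none. The cessation paragraph allows PN to restart within the next 24 hours, and EN interruptions of 2 hours or more trigger the top rate.
- That a definite share of the 100 patients is affected. The document gives neither NN intake nor the distribution of enteral intake.

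**Conclusion.** The inconsistency is real and follows from the text at the 80 % boundary. Exclusion and starting rate count enteral energy alone; review and stopping count enteral plus propofol and glucose energy. Whenever EN is at most 80 % and the sum exceeds 80 %, a patient can be randomised and started on PN at 40 % of requirement, although the same intake meets the stop rule at the first review.

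In the 70 + 15 example the total is 125 %, assuming unchanged intake and PN at the starting rate for 24 hours. The 88 kcal/day figure rests on the assumed 70 kg CBW. The mismatch at 40 % holds only if Fig. 2 keeps that cut. The number affected cannot be derived from the document. It is tempting to read this as a loss of power or a measured dilution of the primary contrast, but no such loss has been computed, and PN may restart on later days, so narrowing is a direction without a size. This is a contradiction between stated rules, worth correcting because correction is cheap; it does not invalidate the trial.

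**What to change.** Reconcile the exclusion criterion, the starting-rate rule, the midday review and the stop rule on one stated energy base: the same named sources, the same 24-hour look-back and the same CBW-based requirement. At minimum, bring the starting-rate rule into line with the review and stop rules. If entry is meant to rest on enteral energy alone, say so and give the reason. Which base applies is for the investigators to decide. Check Fig. 2 against the chosen wording, including any 40 % cut.

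The cost is a short amendment and a change to the screening or dosing worksheet. The propofol and glucose data are already needed for the day-2 review. The downside is small: some patients near 80 % may change eligibility or starting band. The abstract describes the trial as under way, so the date of any change should be recorded.
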